# A Digital Health Innovation to Prevent Relapse and Support Recovery in Youth Receiving Specialized Services for First-Episode Psychosis: Protocol for a Pilot Pre-Post, Mixed Methods Study of Horyzons-Canada (Phase 2)

**DOI:** 10.2196/28141

**Published:** 2021-12-07

**Keywords:** psychotic disorders, mental health, telemedicine, young adult, mental health services, e–mental health, virtual care, schizophrenia, eHealth, social support, therapy, psychiatry, psychology

## Abstract

**Background:**

Psychotic disorders are among the most disabling of all mental disorders. The first-episode psychosis (FEP) often occurs during adolescence or young adulthood. Young people experiencing FEP often face multiple barriers in accessing a comprehensive range of psychosocial services, which have predominantly been delivered in person. New models of service delivery that are accessible, sustainable, and engaging are needed to support recovery in youth diagnosed with FEP.

**Objective:**

In this paper, we describe a protocol to implement and evaluate the acceptability, safety, and potential efficacy of an online psychosocial therapeutic intervention designed to sustain recovery and prevent relapses in young adults diagnosed with FEP. This intervention was originally developed and tested in Australia and has been adapted for implementation and evaluation in Canada and is called Horyzons-Canada (HoryzonsCa).

**Methods:**

This cohort study is implemented in a single-center and applies a pre-post mixed methods (qualitative-quantitative convergent) design. The study involves recruiting 20 participants from a specialized early intervention program for psychosis located in Montreal, Canada and providing them with access to the HoryzonsCa intervention for 8 weeks. Data collection includes interview-based psychometric measures, self-reports, focus groups, and interviews.

**Results:**

This study received funding from the Brain and Behavior Research Foundation (United States), the Quebec Health Research Funding Agency (Canada), and the Canada Research Chairs Program. The study was approved by the Research Ethics Board of the Centre intégré universitaire de santé et de services sociaux de l'Ouest-de-l'Île-de-Montréal on April 11, 2018 (#IUSMD 17-54). Data were collected from August 16, 2018, to April 29, 2019, and a final sample of 20 individuals participated in the baseline and follow-up interviews, among which 9 participated in the focus groups. Data analysis and reporting are in process. The results of the study will be submitted for publication in 2021.

**Conclusions:**

This study will provide preliminary evidence on the acceptability, safety, and potential efficacy of using a digital health innovation adapted for the Canadian context to deliver specialized mental health services to youth diagnosed with FEP.

**Trial Registration:**

ISRCTN Registry ISRCTN43182105; https://www.isrctn.com/ISRCTN43182105

**International Registered Report Identifier (IRRID):**

RR1-10.2196/28141

## Introduction

### Background

Psychotic disorders have a lifetime prevalence of 3% [1] and include symptoms such as delusions, hallucinations, disorganized thoughts and behaviors, poverty of thought and affect, apathy, and deficits in verbal memory and executive functioning [2,3]. The onset of psychosis typically occurs during adolescence or young adulthood (ie, between the ages of 15-25 years), often leading to substantial impairments in social and community functioning, and ultimately derailing transitions toward life goals. Psychosis is associated with three of the top five leading causes of disability in the world (ie, major depression, bipolar disorder, and schizophrenia) for adolescents and young adults [4], incurring substantial costs for the health care system and society in terms of loss of productivity. As such, psychotic disorders have been described in the literature as among the most scientifically challenging and disabling mental disorders [5,6].

Over the past two decades, a specialized early intervention approach has been developed for youth diagnosed with first-episode psychosis (FEP) with the ultimate goal of achieving symptom remission, relapse prevention, and social recovery [7,8]. Many of these programs accept patients with schizophrenia spectrum psychoses and affective psychoses. Specialized early intervention services typically involve medication, psychosocial services (eg, illness education, lifestyle management, employment and education support, or family education and support), and case management [7,8]. The short-term (ie, 1-2 years) benefits of this specialized approach compared to routine care have been reported in several randomized controlled trials, quasi-experimental studies, and reviews of the literature [9-11]. Randomized controlled trials have confirmed that young people treated in a specialized early intervention service have higher rates of adherence; lower relapse and hospitalization rates; better quality of life; and improved outcomes at 12, 18, and 24 months compared to patients in routine care [11-13].

Although the specialized early intervention approach has shown promise in improving outcomes in youth with FEP, the need to develop better psychological, social, and vocational interventions for this population continues to be a priority. This is because there are several clinical challenges associated with treating this population that are of high concern for clinicians, patients, and families. These include high rates of relapse (estimated at 30%) [14,15] and high rates of service disengagement, which range between 20% to 40% across specialized early intervention programs [16,17]. There are also challenges in sustaining improvements in symptoms and global functioning beyond the first 2 years of receiving specialized services [18].

To date, specialized early intervention services have been restricted to models of care that are predominantly delivered in person. However, research suggests that after an initial period of receiving intensive treatment, some youth begin to experience the phenomenon of *overengagement* or *engulfment* by services and prefer a less intensive form of follow-up [17,19]. Moreover, relying entirely on services delivered in person may not be feasible given that specialized early intervention is resource-intensive, with typical case manager-to-patient ratios being 1:25 and services often delivered in the community, which presents a range of challenges including, for example, loss of productivity and lack of access to transportation [20]. Research is needed on new models of service delivery that are accessible, sustainable, engaging, and effective in supporting recovery in youth diagnosed with FEP. This is especially relevant during the first 5 years of the illness as this phase is considered as the “critical period” when clinical and psychosocial interventions have the highest impact [21]. There is also a need for sustainable models of service delivery that can meet the need for psychosocial support beyond the time frame of receiving specialized early intervention for psychosis services.

Information and communication technologies (ICTs) offer a promising avenue for addressing the aforementioned clinical challenges by increasing access and quality of mental health services, and ultimately supporting the process of recovery for youth experiencing FEP [22-25]. These technologies can potentially deliver services using a less intensive and more engaging format that is compatible with the culture of young people growing up in the 21st century. Our prior research conducted in a Canadian specialized early intervention for psychosis setting has shown that more than 90% of youth diagnosed with FEP receiving specialized services have regular access to the internet through computers and mobile devices, and many are receptive to the idea of using these technologies for mental health care [24,25]. However, despite the potential of technology for improving mental health care for youth, this area has received limited research attention in the Canadian field of early intervention for psychosis. Consequently, few studies exist on the acceptability, safety, and efficacy of digital health innovations to support recovery in youth diagnosed with FEP. Country-specific research on digital mental health care is relevant for advancing policy and practice that is contextualized to the needs of a nation’s population. For example, the Canadian health care landscape has particular characteristics that justify locally driven digital mental health service research. According to Martin and colleagues [26], Canada has a health care system that is managed through provincial and territorial insurance plans; a vast geography; and a significant population diversity in terms of density, culture, and language [26]. These characteristics are important considerations for adapting, implementing, and evaluating digital health service innovations in the Canadian context.

### The Horyzons Intervention Platform

Members of our team have developed an innovative web-based therapeutic intervention platform, called Horyzons, designed to sustain the treatment benefits of early intervention for psychosis and to promote long-term social functioning [27]. This intervention delivers evidence- and strengths-based targeted psychosocial interventions and is enhanced by a moderated online social networking environment. Youth diagnosed with FEP are guided through interactive games to identify, discuss, and develop key personal strengths in an online environment and in real life to address relapse risk factors and psychological well-being.

Specifically, Horyzons consists of *interactive psychosocial interventions* that are informed by evidence-based psychosocial interventions targeting key risk factors and salient domains in the early recovery process (including psychoeducation, vocational recovery, early warning signs of relapse, depression, social anxiety, personal strengths). Youth with FEP are prompted to practice newly acquired skills through over 350 purpose-developed behavioral activities, which are designed to bridge the gap between online therapy and real-world outcomes (eg, tips on how to use personal strengths to cope with stress, enhance well-being, or improve social connectedness). Horyzons also includes *peer-to-peer web-based social networking* that includes a web feed (or news feed) where youth with FEP and moderators can post comments and information, upload pictures and videos, and *like* different types of content, and includes *moderation* that is conducted by clinicians and peer support workers.

Clinician moderators provide guidance, monitor clinical status, and ensure safety of the social networking environment. Clinician moderators develop brief case formulations that are presented at weekly supervision meetings with the senior clinical research team. Clinician moderators send each youth tailored content suggestions (eg, step or action) weekly based on the young person’s needs, interests, and strengths. Suggestions appear on the young person’s home page, and they receive a text notification via the intervention platform’s SMS text messaging feature. Peer support moderators are young adults with lived experience who have received peer support training and who have been stable and in remission for a minimum of 2 years. Their role includes assisting with orientation to the Horyzons intervention platform, providing support, and fostering engagement. For example, peer support moderators reach out to new users or users that have not logged into the intervention platform after a week. They also post *icebreakers* and comments, *like* the posts of users, and engage in role modeling activities. They receive supervision from the clinical research team. The integrity of the moderation is ensured through a detailed moderation manual, and all moderators participate in weekly to biweekly group supervision sessions with senior members of the team. The intervention platform includes a comprehensive safety protocol following best practices in internet research involving vulnerable people [28], which considers 3 levels of security (ie, online safety, clinical safety, and system security). This safety protocol (including criteria and the process for withdrawal from the study) was successfully used in previous research on Horyzons [27,29].

### Research and Development of Horyzons and Canadian Adaptations

A detailed description of the intervention, its development, and its subsequent adaptation for the Canadian context can be found in our previous published work [30-32]. The first version of Horyzons was developed iteratively over a 30-month period following participatory design principles involving patients, clinical psychologists, computer programmers, health informatics experts, web and graphic designers, and professional writers. It was then pilot-tested on a sample of 20 young adults for its feasibility, acceptability, utility, and safety considerations over 1 month [27]. Results showed that there were no dropouts and incidents (ie, adverse events or inappropriate use) during the pilot, and system use was high, with a total of 275 log-ins. Specifically, 70% of participants used the system for at least 3 weeks, 95% used the social networking features, and 60% completed at least 3 therapy modules. Moreover, all participants found the system easy-to-use, 70% considered it to be a useful long-term treatment option beyond discharge from early interventions services, 100% considered it to be safe, 85% would recommend it to others, and 100% reported moderation to be helpful. With respect to potential clinical improvements, 70% considered the therapy modules to be helpful, and 60% reported that Horyzons significantly increased their social connectedness. Paired samples *t* tests also revealed a significant reduction in depressive symptoms at follow-up (d=0.60; *P*=.02) [27]. The safety strategy pertaining to the intervention study addressed both static (eg, personality trait variables) and dynamic factors (mental health status), and results indicated no clinical or security problems related to the use of Horyzons during the pilot study [27,33]. Additionally, a second version of Horyzons was evaluated in Australia within the context of a 5-year follow-up randomized controlled trial [29], with results recently published. Horyzons has also been piloted in the United States, and preliminary analyses of within-group effect sizes demonstrated the greatest improvements in psychotic symptoms (d=0.65-0.81), followed by depressive symptoms (d=0.14-0.30) and social functioning (d=0.18) [34]. Horyzons has also been adapted for young people at ultra-high risk for psychosis, and preliminary research suggests that it is effective in improving social functioning in this population [35].

We recently completed a phase 1 adaptation study of the Horyzons intervention platform in two specialized early intervention clinics for FEP in 1 urban and 1 urban-rural setting, in 2 Canadian provinces [30]. The phase 1 study involved a mixed-methods approach, combining descriptive qualitative and quantitative methods, and was informed by the literature on adaptation of psychosocial interventions [31,36]. Data was collected using focus groups, semistructured interviews, and consultations. The main purpose of the phase 1 study was to determine the types of adaptations needed to the website and the therapeutic intervention protocol before implementing the intervention live. Considering participants’ and clinicians’ perspectives on the platform, we adapted the Horyzons intervention for Canada (HoryzonsCa). Specifically, adaptations were made to content on employment, study, and volunteer opportunities, and postdischarge information (eg, finding a family doctor); general use and safety features (eg, terms of use, translation of Australian list of problem words to French, safety protocol); and clinical moderation protocol (eg, clinical notes and supervision structure). However, in this phase 1 study, participants had limited access to all the components of the HoryzonsCa intervention; for example, they had access to the therapeutic content modules but not to clinical and peer support moderation nor were they able to communicate with other participants. Their access was also time-limited to 2 weeks. Thus, we designed this phase 2 pilot protocol to assess the acceptability, safety, and potential efficacy of the HoryzonsCa intervention with all features of the intervention accessible to a target sample of 20 to 25 participants over 8 weeks.

In this paper, we describe the research protocol informing this phase 2 live pilot study of HoryzonsCa. The protocol is largely informed by the Technology Acceptance Model (TAM) [37,38], which is a well-established model focusing on individual perceptions pertaining to ease of use and usefulness of a technology, and the eHealth Adaptation Framework [31], which considers broader factors such as language, culture, and context pertaining to localized implementation of an eHealth innovation. Our attention to the adaptation aspects of Horyzons is in alignment with strategies recommended in the literature to better capture complexities pertaining to the implementation of eHealth innovations [39]. Moreover, during our analysis and interpretation of the results, we will also begin to consider models stemming from sociotechnically informed theories of change at the levels of individual, organization, and system, such as the nonadoption, abandonment, spread, scale-up, sustainability framework, which is intended to facilitate reflection on factors influencing adoption, nonadoption, abandonment, spread, scale-up, and sustainability of eHealth technologies [40]. Such reflections will be important to inform the design of a scaled-up evaluation of the intervention, including the types of data that will be important to collect.

### Objectives and Hypotheses

The aim of this study is to determine the acceptability, safety, and potential efficacy of HoryzonsCa in supporting recovery in young adults receiving specialized services for FEP. Specifically, our objectives are:

To determine the acceptability of an online therapeutic platform (HoryzonsCa). *Primary hypothesis:*
HoryzonsCa will be acceptable to patients. Our conceptualization of acceptability is partially informed by the TAM [37,38], which posits that attitudes toward using a technology influence intention (“acceptance”) to use a technology, which is a direct determinant of behavior [37,38]. The attitude construct is composed of perceived usefulness (an individual’s perception that using an information technology [IT] system will be helpful to them) and perceived ease of use (an individual’s perception that using an IT system will be free of effort) [38]. Patients’ acceptance regarding the use of technologies in health care delivery has been extensively assessed using the TAM model and its derivatives, which highlight the importance of considering factors beyond the individual’s attitudes [41-44]. As such, we also include the concept of adoption in our conceptualization of acceptability, which “is defined as the intention, initial decision, or action to try or employ an innovation or evidence-based practice” [45]. Thus, using this combined understanding of acceptability, in this study, the intervention will be considered acceptable if at least 70% of participants provide positive reports on general experience of the platform, 60% provide positive reports on perceived usefulness (helpfulness), 60% provide positive reports on ease of use, and 60% log onto the site at least 4 times over the 8-week follow-up. These percentages are hypothesized based on the results obtained from the original Horyzons pilot study [27]. We will also determine acceptability through qualitatively assessing perceptions of HoryzonsCa in relation to likes, dislikes, perceived barriers and facilitators to using the platform, and ease of use/experiences of navigating and using its key features (eg, various psychoeducational modules or café) and through exploratory analysis of website use analytics.To assess the safety of the HoryzonsCa platform. *Secondary hypothesis:* HoryzonsCa will be safe, defined as no adverse events, reports, or incidents (eg, hospitalization, suicidal ideation, or disclosure to treatment team regarding harm) related to use of the platform from baseline assessment to 8 weeks follow-up, and at least 70% of participants report that they agree or strongly agree with the perceived safety of the platform and perceived confidentiality of information shared on the platform. We will also determine safety through qualitatively assessing perceptions of the HoryzonsCa platform (eg, experiences, concerns).To assess the potential efficacy of the HoryzonsCa intervention/platform. *Secondary hypotheses:* Participants will show moderate to large improvements (Cohen *d*≥0.5) on measures of social functioning (Social and Occupational Functioning Assessment Scale; Personal and Social Performance Scale) and either improvement of 1 point or no deterioration on the Clinical Global Impression Scale, from baseline to 8 weeks follow-up, as our primary foci for assessing potential efficacy. We will also assess for improvements in social support, self-esteem and perceived strengths, and symptoms. The analysis will help determine pre-post effect sizes on a number of variables conceptually targeted by the platform. These effect sizes will be used in a future clinical trial (eg, randomized controlled trial) for the purpose of statistical power calculation and estimation of sample size.

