#### Safety

*Safety*, which considers 3 levels of security (ie, online safety, clinical safety, system security), was assessed using two specific questions (ie, “I felt safe on Horyzons-Canada” and “I felt like the information shared on Horyzons-Canada was confidential”) in the HC-AUSI-Q. In addition, any adverse events, reports, or incidents (eg, hospitalization, suicidal ideation, or disclosure to treatment team regarding harm) in relation to the use of the online system were carefully monitored and quantified over the study duration. The causal relationship between adverse events and use of HoryzonsCa was determined based on detailed documentation of each event and through discussion by members of the research and moderation team. All adverse events, reports, and incidents (eg, hospitalization, major deterioration in ability to function) were also submitted to the ethics review board for further examination.

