#### Potential Efficacy

In terms of *primary clinical measures*, *social functioning* was measured using the interviewer-administered Social and Occupational Functioning Assessment Scale that comprises a 100-point single item to assess social and occupational functioning [3] and the interviewer-administered Personal and Social Performance Scale that consists of a 100-point single item to assess functioning in four domains: socially useful activities (including work and study), personal and social relationships, self-care, and disturbing and aggressive behaviors [48]. In terms of *secondary clinical measures*, *global improvement and therapeutic response* was assessed using the clinician-administered Clinical Global Impression Scale that consists of two items to assess global improvement and severity of illness [49]. We also assessed *social support* using the self-reported Multidimensional Scale of Perceived Social Support that includes 12 items (eg, “I get the emotional help and support I need from my family) [50]; *self-esteem and perceived strengths* using the self-reported Self-Esteem Rating Scale that consists of 40 items (eg, “I feel that I am a very competent person”) [51], the self-reported Strengths Knowledge Scale that includes 8 items (eg, “I know what I do best”) [52], and the self-reported Strengths Use Scale that consists of 14 items (eg, “I am regularly able to do what I do best”) [52,53]; and *symptoms* using the following interviewer-administered assessments: the Scale for the Assessment of Positive Symptoms that consists of 34 items in four symptom domains (hallucinations, delusions, bizarre behavior, and positive formal thought disorder) [54]; the Scale for the Assessment of Negative Symptoms that includes 25 items in five symptom domains (affective flattening or blunting, alogia, avolition-apathy, anhedonia-asociality, and attention) [55]; the Brief Psychiatric Rating Scale that includes 24 items assessing psychiatric symptoms such as somatic concern, anxiety, depression, and suicidality [46]; and the Calgary Depression Scale that includes nine items assessing depressive symptoms such as depressed mood, hopelessness, and suicide [56].

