## Results

This study was funded by the Brain and Behavior Research Foundation (United States), Quebec Health Research Funding Agency (Canada), and the Canada Research Chairs Program (Canada), and was approved by the Research Ethics Board of the Centre intégré universitaire de santé et de services sociaux de l'Ouest-de-l'Île-de-Montréal on April 11, 2018 (#IUSMD 17-54). The study was registered as a clinical trial at [60] (ISRCTN43182105). Recruitment was initiated on May 10, 2018, and data collection occurred between August 16, 2018, to April 29, 2019. A total of 48 individuals were approached for the study, from which 20 were excluded (17 declined to participate, 1 was not reachable, 1 did not meet inclusion criteria, and 1 met exclusion criteria). The 28 remaining individuals provided informed consent and were invited to complete a baseline assessment, from which 4 did not attend for various reasons (eg, no longer interested, no longer attending clinic, or not feeling well). Among the 24 participants that completed the baseline assessment, 3 dropped out of the study before being given access to the intervention, and 1 was excluded from the intervention soon after team discussion of the baseline assessment due to not meeting inclusion criteria (ie, clinical stability). Upon completion of the baseline assessment and confirmation of eligibility criteria, a final sample of 20 participants were given access to the intervention and none of these were lost at 8 weeks follow-up. Participants were recruited over a 9-month duration (which was 3 times longer than our originally anticipated 3-month timeline), with a recruitment rate of approximately 3 participants per month. A total of 9 participants attended the focus group meetings of approximately 120 minutes each session (4 attended more than once). No adverse events related to the intervention occurred during the live pilot implementation. Further details on the results are expected to be submitted for publication in 2021.

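### The safety rule calls the platform safe on no team-attributed events (plus 70% perceived safety), but zero in 20 people leaves an 8-week risk of up to about 17% open

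*Protocol article*

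**What the plan says.** In the Protocol article, Objectives and Hypotheses, the second objective carries a secondary hypothesis with a definition built in: "HoryzonsCa will be safe, defined as no adverse events, reports, or incidents". The sentence gives hospitalization, suicidal ideation and disclosure of harm to the treatment team as examples, and limits the count to those "related to use of the platform from baseline assessment to 8 weeks follow-up". A second condition is joined by *and*: "at least 70% of participants report that they agree or strongly agree with the perceived safety of the platform and perceived confidentiality". Qualitative assessment of perceived safety is added alongside.

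Under Outcome Measures, Safety, the causal link between an event and the platform is determined from documentation of each event and "through discussion by members of the research and moderation team". The same section adds: "All adverse events, reports, and incidents (eg, hospitalization, major deterioration in ability to function) were also submitted to the ethics review board".

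The Analysis Plan evaluates safety through proportions agreeing with questionnaire items. The Results section reports 20 people given access, none lost at 8 weeks, and "No adverse events related to the intervention occurred during the live pilot implementation".

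Two scales given at both visits bear on suicidality but are listed under Potential Efficacy. One is the Brief Psychiatric Rating Scale (BPRS), which has a suicidality item. The other is the Calgary Depression Scale, described as "nine items assessing depressive symptoms such as depressed mood, hopelessness, and suicide".

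**The concern.** The hypothesis is a decision rule: if both conditions are met, the platform is declared safe. Two features weaken the event condition.

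First, an event counts only if it is judged related, and the judges include members of the moderation team. The section on the Horyzons intervention platform shows that moderators deliver much of the intervention: they guide participants, monitor clinical status and send weekly tailored suggestions. The study has one arm, so no comparison rate can check the attribution.

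Second, a count of zero in about 20 people is weak evidence about a rate. The sample size was set by recruitment feasibility, moderator budget and the need for enough active users, not by safety precision.

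Safety is one of the three stated aims, and the findings are meant to inform a larger study. A conclusion worded as safe would carry forward more assurance than the data give, in a population where hospitalization and suicidality are the events of concern.

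**Working it through.** The article states no tolerable event rate, precision or confidence limit for safety, so there is no figure of its own to reproduce.

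**Inputs**
- Exposed and followed: 20 (Results). The participant flow adds up: 48 − 20 = 28; 28 − 4 = 24; 24 − 3 − 1 = 20.
- Target sample: 20 to 25 (Participants, Sample Size Considerations, Recruitment, and Orientation Process).
- Related adverse events: 0 (Results).

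**Step 1. What zero events can exclude.** With zero events in n people, the exact (Clopper-Pearson) upper limit solves (1 − p)^n = α, so p = 1 − α^(1/n). Take α = 0.025 for a two-sided 95% interval and 0.05 for a one-sided bound.
- n = 20, two-sided: 1 − 0.025^(1/20) = 16.8%
- n = 20, one-sided: 1 − 0.05^(1/20) = 13.9%
- n = 25, two-sided: 1 − 0.025^(1/25) = 13.7%
- n = 25, one-sided: 1 − 0.05^(1/25) = 11.3%

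**Step 2. How often the event condition is met at a given true risk.** The probability of no events is (1 − p)^20.

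| True 8-week risk of a related event | Probability of zero in 20 |
|---|---|
| 1% | 81.8% |
| 2% | 66.8% |
| 5% | 35.8% |
| 10% | 12.2% |

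**Step 3. How many event-free participants a tighter statement needs.** For a one-sided 95% bound no higher than p, n = ln(0.05)/ln(1 − p), rounded up. This gives 29 for 10%, 59 for 5%, 149 for 2% and 299 for 1%. The target of 20 to 25 falls short of even the first.

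**Step 4. What the count contains.** The hypothesis counts related events, the research and moderation team decides which those are, and the Results sentence gives related events only. From the article alone, a reader cannot tell a study with no events from one with several events that were all judged unrelated. The Safety section says that all events were documented and submitted, so the total appears to be available.

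**The case against.** The strongest case on the other side has five parts.

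- **The rule has two conditions and is strict.** Zero related events is necessary but not sufficient, and one related event fails it; at a true risk of 5% it fails about 64% of the time (1 − 0.358). This is correct. But the perceived-safety condition does not measure how often events occur, and a strict rule still does not turn a pass into evidence of a low rate.
- **There is outside scrutiny.** All events "were also submitted to the ethics review board for further examination". A reader might infer that events judged unrelated drop out of sight. The documents do not support that: such events are documented and submitted, and fuller results are deferred to a later paper. What stands is narrower. They do not count towards the defined result, and the article gives the board no part in the relatedness decision.
- **Detail may lie elsewhere.** The adapted safety protocol is in an appendix that is not shown, and an interval or all-event table could be left to a fuller plan. Their absence is therefore not the point. The point is the success definition and the attribution process that the article does print.
- **Limits are admitted.** The article calls its evidence preliminary and asks for caution on safety. That caution is tied to the 8-week follow-up, and the small sample is tied to detecting treatment effects. Neither addresses what zero in 20 means.
- **All-event counts are hard to read in one arm.** This stands. The Introduction cites relapse of about 30% without a period. Assuming a constant hazard, 30% over one year is 1 − 0.7^(8/52) = 5.3% in 8 weeks, about one person in 20. Over two years it is 2.7%, about half a person. Background illness alone could produce events, so the all-event count should accompany the related count, not replace it.

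Two other inferences go too far. The 70% bar lies below the 100% who considered the original pilot's platform safe, but that is not an error, and not agreeing with an item is not the same as feeling unsafe. Nor is suicidality left out: suicidal ideation is a named example of a counted incident.

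**Conclusion.** The concern holds in this form: meeting the rule would not justify the conclusion it is defined to deliver. Zero related events in 20 people is compatible with a true 8-week risk of up to 16.8% (two-sided) or 13.9% (one-sided), roughly one participant in six or seven. Recruiting 25 would have changed this little.

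The figures rest on three assumptions. Each participant contributes one yes-or-no outcome over 8 weeks. Participants are independent; on a shared social network positive dependence is possible, and it would make these limits too optimistic. The attribution is taken as correct, so the limits apply to events judged related. The Results sentence speaks of adverse events; the limits apply to the full condition only if related reports and incidents were also zero. Whether 14% to 17% is too high is a judgement, because the article sets no tolerable rate.

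Nothing here shows that the platform is unsafe or that the attribution was wrong. The defect is in the rule and the word it licenses. It should be corrected before results are reported, though safety is a secondary hypothesis.

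**What to change.** 1. Report all adverse events, reports and incidents from baseline to 8 weeks regardless of attribution: the number of events, and the number of participants with at least one, with an exact 95% confidence interval for the participant proportion.
2. Beside it, report the related-event count in the same form with its exact interval, and state who made the attribution.
3. If the related count is zero, replace the conclusion that the platform is safe with: no related events were observed; rates up to about 17% are not excluded.
4. Keep the perceived-safety proportions as a separate result about user experience.
5. Optionally, add a descriptive count of participants whose BPRS suicidality item or Calgary suicide item worsened between the two visits. This needs no attribution judgement.

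The cost is analysis and wording only, since the article indicates that these data were collected. The headline becomes less favourable. The all-event count mixes background illness with any platform harm, which is why both counts need to be shown together.
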